**Primary objectives**

1. To assess the change in Faecal Egg Counts (FEC) in school age children 14 days following the treatment with a single dose 400 mg of albendazole
2. To monitor efficacy by determining the Cure Rate (CR) and Egg Reduction Rate (ERR)

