### **Parasitological technique to determine FEC**

The standard coprological technique to be used will be the McMaster method, a user-friendly method widely practiced in Veterinary Medicine. The McMaster method is a quantitative method for analysis of FEC. For each sample one chamber (two compartments) will be counted (sensitivity of 50 eggs/gram) (Annex 2.1). A video showing the McMaster technique will be made and provided to all participating laboratories.

McMaster slides will be provided free by the coordinating group

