## **Efficacy study**

### Experimental design

Following obtaining informed consent, schoolchildren in the target age range group will be recruited and asked to provide a recent stool sample (an interval of less than 4 hours) that will be processed to determine the FEC for each STH present. A small subsample of faecal samples will be also collected for coproculture to identify the hookworms species present and preserve parasite material for subsequent analysis (Annex 2.3).

All children providing stool samples will be treated with Albendazole (GSK®) single tablet of 400mg under supervision (chewing + water). The Albendazole will be provided (free) by the coordinating group.

14 to 30 days after treatment a second faecal sample will be collected from the children to determine again FEC. Only children infected with a minimum of 150 eggs/gram of any species of STH (i.e. *Ascaris* or hookworms or *Trichuris*) at the first sampling should be included in the second sampling. However, for the other STH present FEC should also be determined at the second sampling.

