### Data analysis

Both CR and ERR will be considered to monitor to efficacy.

To avoid distortion due to the density dependant effect, the CR and ERR will be also calculated separately in the different classes of intensity at baseline.

---

 Statistical power analyses, based on random simulations of correlated overdispersed FEC data reflecting the variance-covariance structure in a selection of real FEC data sets, suggest that a sample size of up to 200 individuals ( $\alpha = 0.05$ , power = 80%) is required to detect a 10 percentage point drop from a null efficacy of  $\sim 80\%$  (mean percentage FEC  $\Delta$  per individual) over a wide range of infection scenarios. Standard power analyses for proportions also indicate that the detection of a  $\sim 10$  percentage point drop from a null cure rate requires sample sizes ranging up to 200 (the largest samples being required to detect departures from null efficacies around 50%). Given an anticipated non-compliance rate of 25%, a sample of 250 individuals with  $>250$  egg/g pre-treatment should therefore be followed up for post-treatment FEC data at each study locality.

The following indexes should be used to monitor drug efficacy:

Cure rate

$$[N \text{ egg positive post-treatment} / N \text{ egg positive pre-treatment}] * 100$$

Mean FEC  $\Delta$  per individual

$$\frac{\sum_{i=1}^{i=N} [T1_i - T2_i]}{N}$$

Where T1 = pre-treatment FEC, T2 = post-treatment FEC, and  $i$  = the  $i$ th subject.

Mean percentage FEC  $\Delta$  per individual

$$\frac{\sum_{i=1}^{i=N} \{ [T1_i - T2_i] / T1_i \} * 100}{N}$$

Percentage  $\Delta$  in the sample mean FEC

$$\{ [\text{sample mean T1} - \text{sample mean T2}] / \text{sample mean T1} \} * 100$$

Confidence intervals for these indexes can be generated by a standard method for proportions in the case of cure rate (the exact binomial method) and by bootstrap resampling methodologies for the FEC  $\Delta$  indexes.

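### The printed cure-rate formula gives the percentage still egg-positive, so a primary efficacy index runs in the wrong direction

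*Protocol*

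**What the plan says.** The second primary objective is "To monitor efficacy by determining the Cure Rate (CR) and Egg Reduction Rate (ERR"). Under Data analysis, the list headed "The following indexes should be used to monitor drug efficacy" opens with the cure rate. Its numerator is the number "egg positive post-treatment} / N" and its denominator the number "egg positive pre-treatment", multiplied by 100. The same section assigns this index "a standard method for proportions in the case of cure rate (the exact binomial method"), and asks for cure rate again within classes of baseline intensity. No other definition of cure appears in the protocol.

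Three other places bear on the point:

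- **Sample-size footnote.** It sizes the study to detect a fall of about 10 percentage points in cure rate from its null value, with up to 200 children needed, and anticipates 25% non-compliance.
- **Experimental design.** "Only children infected with a minimum of 150 eggs/gram of any species of STH" at the first sample go on to the second. The other species present are counted then as well.
- **Parasitological technique.** "For each sample one chamber (two compartments) will be counted (sensitivity of 50 eggs/gram"), so a baseline count of 50 or 100 eggs per gram is positive but below 150.

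**The concern.** A cure rate should rise as the drug works better. The printed ratio falls, reaching 0% when every child is cured and 100% when none is. It contradicts its own label and the footnote. It also contradicts the percentage egg-count indexes printed beside it, which use (T1 − T2)/T1 and increase with efficacy.

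The protocol is to be applied in seven countries, and its overall objective is to develop and validate a standard monitoring method. If some sites follow the formula and others the label, their cure rates are not comparable. At extreme values the mistake would be noticed, but near 50% it would not: a true 40% is reported as 60%, which is plausible for either quantity.

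**Working it through.** **1. The plan's own figure.** The footnote gives up to 200 children for a 10-point fall in cure rate, the worst case being near 50%. Inputs: null 50%, alternative 40%, power 80%, alpha 0.05. The footnote states alpha and power for the egg-count simulations; I assume that they apply to cure rate too, and that the test is two-sided.

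n = [(z₁√(p₀(1−p₀)) + z₂√(p₁(1−p₁))) / (p₀−p₁)]²
= [(1.960 × 0.500 + 0.842 × 0.490) / 0.10]² ≈ 194.

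An exact binomial test first reaches 80% power at 199 and holds it from 210. The figure of 200 is reproduced. The same n results if the index is turned round, because a fall in cure from 50% to 40% is a rise in persistence from 50% to 60%. The sample size is therefore unaffected by the formula; the contradiction lies in the stated direction of change.

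**2. The printed formula.** Take 200 children positive at baseline, all re-sampled, with exact (Clopper-Pearson) 95% intervals.

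| True cure | Still positive | Printed formula | Correct cure rate |
|---|---|---|---|
| 95% | 10/200 | 5.0% (2.4 to 9.0) | 95.0% (91.0 to 97.6) |
| 80% | 40/200 | 20.0% (14.7 to 26.2) | 80.0% (73.8 to 85.3) |
| 70% | 60/200 | 30.0% (23.7 to 36.9) | 70.0% (63.1 to 76.3) |
| 50% | 100/200 | 50.0% (42.9 to 57.1) | 50.0% (42.9 to 57.1) |
| 40% | 120/200 | 60.0% (52.9 to 66.8) | 40.0% (33.2 to 47.1) |

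The printed value is 100 minus the cure rate, and its interval is the mirror image of the right one. They agree only at 50%. A loss of efficacy from 80% to 70% appears as a rise from 20% to 30%.

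**3. A caution for the rewording.** Suppose that the direction alone were flipped and the denominator were every child positive at baseline, re-sampled or not. With 250 eligible children and 25% not re-sampled (an assumption about what non-compliance means), 250 × 0.75 = 187.5, say 188, are re-sampled. At 80% cure, 0.20 × 188 = 37.6, say 38, are still positive. Then:

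- flipped ratio: 1 − 38/250 = 84.8%;
- among re-sampled children: 150/188 = 79.8%.

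The gap is about 5 points, because children without a second sample are counted as cured. Children below 150 eggs per gram for every species would add to it; the protocol does not give their number.

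**The case against.** The best defence is that nobody would be misled. The label, the heading of the list and the footnote all show which way the index should run. Subtracting each reported value and limit from 100 restores the right result with no loss of data, and the sample size stands. All of that is true, and it limits the harm. It does not make the formula correct: the protocol prescribes the calculation, for a primary index, and offers no other definition.

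A reader might infer something stronger: that the denominator is also wrong, because it takes in children who are never re-sampled, and that cure is therefore overstated. The documents do not support this as an effect of the plan as written.

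- The formula names no analysis set, and nowhere is it said that children without a second sample are counted.
- Children unable to give follow-up samples are excluded, the target sample consists of children at or above the 150 threshold, and the individual-level egg-count indexes are paired. These favour a paired reading.
- The threshold applies to any species. A child with 100 eggs per gram of *Trichuris* and 500 of *Ascaris* is re-sampled and can contribute to the *Trichuris* result. Only children below 150 for every species are left out.
- The footnote says that 250 children should be followed up, so its 25% need not mean loss after treatment.

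The inflation in step 3 needs a half-correction that the protocol does not propose. What stands is that the denominator is not spelt out and should be when the line is rewritten. The same holds for the numerator, which is not expressly limited to children positive for that species at baseline.

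**Conclusion.** The formula is wrong as printed and must be corrected. It returns the percentage still egg-positive under the name of cure rate: at 80% cure and 200 children, 20.0% (14.7 to 26.2) in place of 80.0% (73.8 to 85.3). This follows from the formula alone; the 200 is an illustration that sets only the width of the intervals. The distance between printed and true value depends on efficacy, being 90 points at 95% cure, 60 at 80% and nil at 50%.

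The denominator is a secondary matter of wording. The shift of about 5 points at 80% cure depends on a literal reading that the protocol does not require, and on taking the 25% non-compliance as follow-up loss.

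**What to change.** Replace the cure-rate line under Data analysis with a definition for each species:

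CR = 100 × (children egg-positive for the species at baseline and egg-negative for it after treatment) / (children egg-positive for the species at baseline with a post-treatment result).

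State that the exact binomial interval is computed on these two counts, and use the same definition within the baseline intensity classes. This corrects the direction, ties numerator and denominator to the same children, and keeps a child newly positive for a species out of that species' result.

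The cost is one formula and one sentence. No new data are needed and the sample size does not change. Any site that has already applied the printed formula should recompute from its paired results.

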## **Ethical considerations**

### Ethical Committee Review

An overall Ethical clearance for the study was obtained from the Human Research Ethics Committee of the University of Ghent, is submitted at the Queensland Institute for Medical Research, and from the respective research ethics committees of the 6 Countries (Brazil, Cameroun, India, Vietnam, Zanzibar & Ethiopia) involved in this multicentric study.

### Informed consent and enrolment

The Principal Investigators will prepare an Informed Consent Document and submit it to National research ethics committees of the respective countries, and to the Human Research Ethics Committee of the University of Ghent for approval. The consent form will be written in English and translated into each of the local language (sample attached in the Annex). Prior to the trial in the selected study sites, public meetings will be held with the parents/guardians, community leaders and teachers, where the purpose of the trial, safety precautions and benefits for the study population will be explained by qualified study staff. It will be emphasized that participation in the trial is entirely voluntary; neither the parents/guardians nor their children will be discriminated against in any way if they choose not to enter their children into the trial. Prior to agreement to enrol their children in the trial, parents/guardians will be given every opportunity to have their questions answered. Then the parents/guardians will be asked to sign the informed consent document. After signing, one copy of the document will be given to the parent/guardian, while the other will be brought to the study site on the day of enrolment to verify that consent has been given.

### Confidentiality

The information obtained during the conduct of this study will remain confidential. Disclosure of any of the data to third parties other than those allowed in the Informed Consent form will not be permitted. The results of the research study may be published, but subjects' names or identities will not be revealed. Records will remain confidential. To maintain confidentiality, the Senior Scientist will keep records in locked cabinets and the results of the tests will be coded to prevent identification of the volunteers. Access to data entered into computerized files will be permitted only for authorized personnel directly involved with the study and will be password protected. Subject-specific information may be provided to responsible local medical personnel only with the subject's permission. Stool samples collected will not be used for research purposes other than those outlined in the protocol, and will be safely disposed of after the completion of the study.

### Feed-back after the trial has been completed

At the end of the trial, the results of the study will be communicated to the Ministry of Health (MoH) of each study site. In addition, the MoH and Ministry of Education (MoE) officers in charge of the districts where the study had been performed will inform the community of the results through the most appropriate channel, for example, a newsletter or a public meeting. The Department of Control of Neglected Tropical Disease at WHO, Geneva, will coordinate the international dissemination of the study results, including publication.

### Safety

This trial will only use original albendazole product that has already been approved by the National Regulatory authority of each country in which the trial will be carried out. It is recognized that all study sites have been regularly using albendazole or mebendazole in National mass deworming campaigns. The drugs will only be administered by qualified health professionals as outlined in the study protocol. Although treatment with albendazole

has been ongoing as a Public Health intervention, and the safety of the drug in the study group has been well demonstrated, referral to appropriate medical professionals will be made available for any rare but possible severe adverse event occurring during the study will be provided by the study team.

### Benefits

Children participating in the trial will directly benefit by being investigated for STH infections and receiving appropriate treatment. Children still infected at the end of the observation period will immediately be offered additional treatment according of their specific clinical situation. The study results will help to guide WHO and the international scientific community in choosing the most effective protocol to monitor anthelmintic efficacy, and will also guide global recommendations for STH endemic countries.

Klinische Biologie, Microbiologie en Immunologie  
[name]  
Prof. dr. [name]  
ALHIER

COMMISSIE VOOR MEDISCHE  
ETHIEK

## **Annex 2**

### **Parasitological techniques**

## Annex 2.1 - McMaster technique

The McMaster technique uses a counting chamber which enables a known volume of faecal suspension ( $2 \times 0.15$  ml) to be examined microscopically. Thus, if a known weight of faeces and a known volume of flotation fluid are used to prepare the suspension, then the number of eggs per gram of faeces (FEC) can be calculated.

The quantities are chosen so that the faecal egg-count can be easily derived by multiplying the number of eggs under the marked areas by a simple conversion factor.

The McMaster chamber has two compartments, each with a grid etched onto the upper surface. When filled with a suspension of faeces in flotation fluid, much of the debris will sink while eggs float to the surface, where they can easily be seen and those under the grid counted.

[figure not shown]

### Equipment List

- \* Two beakers or plastic containers
- \* Balance
- \* Tea strainer
- \* Measuring cylinder
- \* Stirring device (fork, spatula, tongue depressor)
- \* Pasteur pipettes and rubber teats
- \* Flotation fluid (density of 1.22): to be prepared at least one day before use and kept at temperatures  $> 20^{\circ}\text{C}$ . The flotation fluid is a saturated salt solution, with a minimum of 333 g NaCl in 1L of aq dest; the presence of a salt sedimentation confirms saturation
- \* McMaster counting chamber
- \* Compound microscope

### Procedure

1. Weigh 2 grams of faeces in a plastic beaker (100 ml).
2. Add 30 ml of the flotation fluid saturated salt solution,
3. Homogenise and pour the faecal suspension 3 times through a tea strainer to withhold the large debris.
4. Homogenise the filtrate by pouring it at least 5 times from one beaker to another and fill up one side of a regular McMaster counting chamber by using a pasteur pipette. Repeat for the other side.
5. Allow the counting chamber to stand for 2 minutes, place under a light microscope and examine using a 100x magnification. All the eggs under the two separate grids are counted (this represents a volume of  $2 \times 0.15$  ml)
6. The number of eggs per gram of faeces is obtained by multiplying the total number of eggs under the two grids by 50. The sensitivity of the test is 50.

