**Secondary objectives**

1. To evaluate the suitability of the Faecal Egg Count Reduction Test (FECRT) as a standard tool to monitor efficacy i.e. to develop a robust analytical approach that accounts for possible confounding factors
2. To compare the relative performance of the Kato Katz or other qualitative coprological techniques and the McMaster egg counting technique.

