### **Preliminary Comparative study of the coprological techniques**

As there has been relatively little use of the McMaster method for human coprologic examination, a pilot study comparing the Kato Katz (Annex 2.2) and McMaster method (Annex 2.1) should be undertaken on 200 samples at each study site. From the 200 samples at least 100 samples should be positive for STH in either technique at each study site.

As the Kato Katz method has an estimated sensitivity threshold of 24 eggs/gram of faeces, two McMaster chambers (4 compartments, sensitivity of 25) will be counted for the comparative study.

In the case that the local routine coprological technique is not the Kato Katz , the McMaster method should be compared with the routine technique in use.

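### Annex 2.1 adds 30 ml of fluid to 2 g of faeces but uses a factor of 50 that is exact only for a 30 ml total, so non-zero McMaster counts read about 5–8% low

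*Protocol*

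**What the plan says.** The procedure in Annex 2.1 weighs 2 g of faeces (step 1) and continues "Add 30 ml of the flotation fluid saturated salt solution" (step 2). The suspension is strained and loaded. Then "All the eggs under the two separate grids are counted", a volume given as 2 × 0.15 ml. Eggs per gram come from "multiplying the total number of eggs under the two grids by 50", and the annex adds "The sensitivity of the test is 50". Nothing tells the laboratory to make the suspension up to a total of 30 ml.

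The introduction to Annex 2.1 says that the quantities are chosen so that the result follows from "multiplying the number of eggs under the marked areas by a simple conversion factor". It does not say that 50 is rounded.

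The same basis carries into the pilot, where "two McMaster chambers (4 compartments, sensitivity of 25) will be counted for the comparative study". The section on the parasitological technique repeats the figure of 50 for one chamber.

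**The concern.** A conversion to eggs per gram has to use the total volume in which the eggs are suspended. Here 50 fits the volume of fluid added, which is smaller than the total. The error runs in one direction and would be the same in kind at every site, so more samples or more sites would not average it out.

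It matters for results on the absolute epg scale. The Data analysis section lists the mean FEC change per individual in absolute units, and it asks for cure rate and egg reduction rate by baseline intensity class. A secondary objective is "To compare the relative performance of the Kato Katz" and other techniques with McMaster. Kato-Katz converts from faecal mass alone and has no dilution term, so an offset in the McMaster scale enters that comparison on one side only. The overall objective is to validate a standard protocol, so later users would copy the step.

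**Working it through.** **Inputs from the Protocol.** Faeces m = 2 g, fluid added 30 ml, and volume counted v = 0.30 ml for one chamber (Annex 2.1). Two chambers double this to 0.60 ml. Stated factors: 50 (Annex 2.1) and 25 (pilot section).

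**Formula.** Factor = V/(m × v), where V is the total suspension volume.

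**The plan's own figures.** V = 30 gives 30/(2 × 0.30) = 50 and 30/(2 × 0.60) = 25. Both are reproduced exactly, and only by V = 30 ml.

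**Volume of 2 g of faeces.** The Protocol states no density. The Kato-Katz templates in Annex 2.2 imply some, as nominal mass divided by hole volume:

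- 9 mm × 1 mm: 63.6 mm³ for 50 mg, or 0.79 g/ml
- 6 mm × 1.5 mm: 42.4 mm³ for 41.7 mg, or 0.98 g/ml
- 6.5 mm × 0.5 mm: 16.6 mm³ for 20 mg, or 1.21 g/ml

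Two further cases are assumptions: 1 g/ml, and a case in which only the water in the stool (taken as 75%, so 1.5 ml) adds volume.

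**Steps as written, volumes additive.** Bias = 30/V − 1.

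| Case | Volume of 2 g (ml) | V (ml) | Factor, one chamber | Factor, two chambers | Bias | 2 eggs (epg) | 3 eggs (epg) |
|---|---|---|---|---|---|---|---|
| Water only | 1.50 | 31.50 | 52.5 | 26.3 | −4.8% | 105 | 158 |
| 1.21 g/ml | 1.66 | 31.66 | 52.8 | 26.4 | −5.2% | 106 | 158 |
| 1 g/ml | 2.00 | 32.00 | 53.3 | 26.7 | −6.3% | 107 | 160 |
| 0.98 g/ml | 2.03 | 32.03 | 53.4 | 26.7 | −6.3% | 107 | 160 |
| 0.79 g/ml | 2.54 | 32.54 | 54.2 | 27.1 | −7.8% | 108 | 163 |

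**What cancels.** Multiply every count by k. The percentage change per individual is (kT1 − kT2)/(kT1), so k drops out. The same holds for the percentage change in the sample mean. Cure rate depends only on zero versus non-zero. In a simulated set of 250 children, factors 50 and 53.33 gave the same results: 80.66% change in the sample mean, 80.22% mean individual change, and 14.8% egg-negative.

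**What does not cancel.** The mean absolute change is k times the mean difference in counts. In the same simulated set it was 1184.2 epg with 50 and 1263.1 epg with 53.33, and 1184.2/1263.1 = 0.9375, which is 6.25% low. A child near an epg class limit can fall in a different class, so class-specific results are not strictly immune. The Protocol gives no class limits, so this cannot be sized.

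**The 150 epg rule.** Counts are whole eggs. In every row 2 eggs stay below 150 and 3 eggs reach it. The rule means at least 3 eggs under any of these factors.

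**Against Kato-Katz.** The pilot sets 25 beside 24, and 25/24 = 1.04. At V = 32 ml it would be 26.7/24 = 1.11.

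**The case against.** The best defence is that 50 is a deliberate simplification. Annex 2.1 starts from a known weight of faeces and a known volume of fluid and aims for a simple multiplier. The Protocol then uses 50 and 25 consistently, and no two statements of the factor disagree. A different factor needs a stool density that the Protocol never gives. Displacement varies with water content, and the straining in step 3 removes some solids. Three of the four listed indexes are untouched, and the sample-size footnote rests on percentage change and cure rate. The offset is also small beside counting error: a count of 3, if Poisson, has a relative standard error of 1/√3 = 58%.

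Most of this stands, and it is why the point is minor and its size is a range. The claim of a declared simplification does not stand. The annex says that the quantities were chosen to make the simple factor work, and with 30 ml added they do not. Uncertainty over density changes the size but not the sign.

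A reader might also infer that McMaster will visibly find fewer eggs than Kato-Katz. The Protocol does not support that. Annex 2.2 allows three templates whose implied densities differ by a factor of about 1.5 (1.21/0.79). If true density were 1 g/ml everywhere, the 50 mg template would deliver 63.6 mg and read 27% high, while the 20 mg template would deliver 16.6 mg and read 17% low. In the second case McMaster, at 6% low, would read higher than Kato-Katz. The 24 epg quoted for the pilot points to the 41.7 mg template, where the offset could show. But templates need only be standardised within a country, and sites may compare McMaster with another routine technique.

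**Conclusion.** The point holds and is minor. With the steps as written, non-zero McMaster counts are understated by about 5–8%, and by about 6% at 1 g/ml. This assumes additive volumes and 1.5–2.5 ml for 2 g of faeces, and it leaves out any eggs held back by the strainer. Zero counts stay zero.

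The offset affects the mean absolute FEC change per individual, epg-based intensity classes and the quantitative comparison of methods.

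Two stronger readings are not supported:

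- **The efficacy estimates are biased.** The overall cure rate and both percentage indexes are unchanged. Primary objective 1 speaks of change in FEC without saying that it is absolute.
- **The entry threshold is really about 160 epg, so the wrong children are followed up.** Only the label moves, because the rule selects children with at least 3 eggs either way. The sample-size footnote's own figure of more than 250 epg would be sensitive (5 eggs is 250 at factor 50 and 267 at 53.3). That figure differs from the 150 in the main text, which is a separate matter.

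**What to change.** Reword step 2 of the Annex 2.1 procedure so that the 2 g of faeces is brought up to a total volume of 30 ml with flotation fluid, which takes about 28 ml at 1 g/ml. Keep the factors 50 and 25 and the stated sensitivities. Show the same step in the training video.

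The cost is one sentence. The equipment list already includes a measuring cylinder. Under additive volumes this removes the offset whatever the stool density. In the water-only case, if 0.5 ml of solids were strained out, a residual of about 1.7% in the other direction would remain (29.5/0.60 = 49.2, and 50/49.2 = 1.017).

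Keeping 30 ml of added fluid and changing the factor to 53.3 is the weaker option. It would fix a density that the Protocol does not state, and it would change the sensitivities given in the technique section, the pilot section and Annex 2.1.
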